### Data management

#### Database

The backbone of this Swiss-based study is the IT-infrastructure of the MEM Research Center, University of Berne, which has developed and improved documentation systems and questionnaires over decades.

Orthopaedic spinal units, rehabilitation centres, and pain clinics in CH and NZ will participate in this study. Collaborators in the main clinics will act as local coordinators in association with local research nurses. The outcome assessment is based on physician- and patient-derived data.

After written informed consent patients will be examined by the surgeons or physicians under whose care they are. Research nurses will hand out self-assessment questionnaires to the patients and will be available to help completing these questionnaires if necessary. The completed patient-based questionnaires will be collected by the research nurses and, together with physician-based questionnaires, forwarded to the MEM Research Center in CH respectively to the University of Otago in NZ. All data will be saved at the central database of the main server at the University of Berne.

#### Data security

The computerised medical data collected at the MEM Research Center do not contain names. Only the patient number will be able to connect the names and the medical information at the treatment level. The servers have firewalls and data encryption, and are located in a physically secure environment.

### Statistical Analysis

#### Outcomes

In this prospective cohort study, two interventions for CLBP are compared: surgical and conservative treatment. Subgroups of different surgical treatments can be distinguished. Nonsurgical co-interventions may have an effect on patient groups with surgical as well as with conservative treatment.

Follow-up data at six months will be analysed according to the intention-to-treat principle, except for those patients who change treatment groups before the beginning of the allocated treatment.

Changes in dependent outcome variables between baseline and follow-up at six months will be analysed by multiple linear regression models. Surgical and conservative treatment, patient characteristics, and co-interventions are independent variables. To address potential effect modification, we will then incorporate interactions between type of treatment and the different co-interventions and patient characteristics.

Highest priority among co-interventions will be given to the analysis of effects of cognitive behavioural therapy and return-to-work programs. Among patient characteristics highest priority in data analysis will be given to gender, age, and duration of work-absenteeism.

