These trials showed conflicting results, with no treatment being clearly superior [18]. Exclusion criteria in all these trials were restrictive; for example, patients with mild CLBP and no need for surgery, as well as patients with progressive neurological abnormalities and surgery were excluded. Recruitment in all trials was long and varied between four and six years. This leads to a reduced generalizability of the results.

The analysis of data from an observational cohort with adequate statistical methods can lead to results with an evidence level 2++. It is slowly recognized that for certain clinical questions RCTs have limitations [19] and may be unnecessary, inappropriate, or impossible to conduct [20].

Feasibility is an important aspect and has been highlighted by the SPORT trial, which consists of a randomised and an observational cohort. The rate of surgical patients with treatment crossover within two years of treatment allocation was 40% in the RCT, compared to merely 4% in the observational cohort [17,21]. The comparable rates of conservative patients' crossover to surgery were 45% and 22%. Currently, a prospective cohort study comparing patients with lumbar fusion and patients with multidisciplinary therapy is under way, for which a randomised cohort design was planned, but was changed to an observational design to minimise a treatment crossover [22].

Therefore, we chose to conduct a prospective observational cohort study as well, with a lower level of evidence than an RCT though, but a higher feasibility.

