#### Conservative treatment and co-interventions

We defined the absence of a surgical treatment as conservative treatment. Different conservative treatments are considered as co-interventions. These co-interventions that also can be applied to the surgical patient group are biomedical, psychologically oriented (cognitive behavioural therapy), and socio-occupational interventions (return-to-work program). Biomedical interventions include physical treatments, exercise therapy, manual therapy, back schools, pharmacological procedures (analgetics, NSAID, opioids, antidepressants), and invasive nonsurgical treatments (acupuncture, injections, facet/nerve root blocks, neuroreflexotherapy, percutaneous electrical nerve stimulation, radiofrequency, intradiscal electrothermal therapy, intradiscal radiofrequency thermocoagulation, cryotherapy of the facets, alcohol denervation, temporary epidural catheters, permanent intrathecal pain-control pumps, and spinal cord stimulators).

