#### Outcome measures

Relevant outcomes are identified as scores organised in categories of answers in standardised multi-dimensional assessment tools. Significance of outcomes is defined by effect sizes (i.e. differences between treatment groups in changes from baseline to endpoint, typically divided into three groups: short-, medium-, and long-term changes of respective scores). For this study, outcome measures will be assessed at six-month follow-up. Longer follow-ups may result in difficulties for the identification of effect modifiers [23].

ODI [24,25], SF-36 [26], EQol-5D [27], and pain measured by VAS [28] are among the most frequently used outcome assessment measurements of CLBP. All of them are valid and reliable. In this study, the primary endpoint at six-month follow-up is ODI. Key secondary endpoints are SF-36, EQol-5D, and VAS.

Other secondary outcomes that will be collected by patient self-assessment are onset/duration/recurrence of LBP [29-31], work/disability compensation status [32,33], duration of work-absenteeism [34], location and number of other painful body sites [35,36], interference of LBP with work and/or activity, symptom-specific well-being, general well-being, and satisfaction with treatment.

Physician-based assessment of secondary treatment outcomes at six-month follow-up include rate/type/therapeutic consequences of complications [37], change in medication, and overall outcome (McNab criteria).

Given the nature of interventions, blinding is not feasible. Outcome assessments are based on standardised, reliable, valid tools.

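### The intention-to-treat rule covers complications, so surgical complications after a switch from conservative care count as conservative and shrink the between-group harm contrast

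*Protocol article*

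**What the plan says.** Four statements in the protocol article bear on this point.

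- **Analysis rule** (Statistical Analysis, Outcomes): "Follow-up data at six months will be analysed according to the intention-to-treat principle". The one exception is for patients who switch before their allocated treatment starts. No outcome is singled out.
- **Complications** (Outcome measures): "Physician-based assessment of secondary treatment outcomes at six-month follow-up include rate/type/therapeutic consequences of complications". They are a secondary outcome, but not one of the key secondary endpoints.
- **Treatment definition** (Conservative treatment and co-interventions): "We defined the absence of a surgical treatment as conservative treatment".
- **Crossover seen elsewhere** (Background). A cited study had a randomised and a non-randomised cohort. Among its surgical patients, switching within two years was 40% and 4% respectively. For switches the other way the article says: "The comparable rates of conservative patients' crossover to surgery were 45% and 22" (per cent, with the non-randomised cohort second).

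The article has no separate sentence on how complications are assigned to a treatment group.

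**The concern.** Intention to treat is a reasonable choice for ODI and the other effectiveness scores. For a harm that arises from a procedure, it credits the event to the group in which the patient began. If conservative care starts and surgery follows in, say, month 3, a complication of that operation is counted as conservative. The exception does not reach this patient, because the allocated treatment had already begun.

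The same patient does not fit the article's definition of conservative treatment, since surgery took place. The two sections therefore put one patient in two different groups, and the conflict matters most for surgical harm.

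Such switches are foreseeable. Patients enter after a year of conservative treatment without relevant improvement, treatment may last up to six months, and the Background reports crossover to surgery in a comparable cohort. The article hopes to influence guidelines and to help avoid unnecessary operations, so a diluted harm contrast would work against its purpose.

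**Working it through.** **1. The article's own denominator.** Feasibility of the study: 2200 × 0.75 = 1650 eligible; 1650 × 0.60 = 990 enrolled; 990 × 0.80 = 792 analysed under intention to treat. This reproduces the stated 792. With the 1:1 split assumed in the sample size section, that is 396 per group.

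**2. Inputs for the dilution.**
- c = share of conservative patients operated on after starting conservative treatment. The article gives no six-month value. The range used is 5%, 11% (half of 22%) and 22% (the cited observational cohort).
- ps, pc = complication risk with and without surgery. The article gives neither, so both are assumptions. The illustration uses 15% and 3%.
- Operated crossovers are assumed to have the same risk ps as patients operated on first.

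**3. Formula.**
- Surgical group under the stated rule: ps.
- Conservative group under the stated rule: c × ps + (1 - c) × pc.
- Difference: ps - [c × ps + (1 - c) × pc] = (1 - c) × (ps - pc).
- Difference by treatment received, under these assumptions: ps - pc.

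The ratio of the two differences is 1 - c, whatever ps and pc are.

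**4. Numbers, with ps = 15% and pc = 3%** (true difference 12 points, true risk ratio 15/3 = 5).

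| c | Conservative group as reported | Difference (points) | Factor | Risk ratio |
|---|---|---|---|---|
| 5% | 0.05 × 15 + 0.95 × 3 = 3.6% | 11.4 | 0.95 | 15/3.6 = 4.2 |
| 11% | 0.11 × 15 + 0.89 × 3 = 4.3% | 10.7 | 0.89 | 15/4.32 = 3.5 |
| 22% | 0.22 × 15 + 0.78 × 3 = 5.6% | 9.4 | 0.78 | 15/5.64 = 2.7 |

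**5. Share of surgical complications listed under conservative care.** With equal groups this is c/(1 + c): 0.05/1.05 = 5%, 0.11/1.11 = 10%, 0.22/1.22 = 18%. For example, with ps = 10%, 396 per group and c = 22%, the conservative group carries 396 × 0.22 × 0.10 = 8.7 of 39.6 + 8.7 = 48.3 surgical complications.

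**The case against.** **The rule may not have been meant for complications.** The sentence is general and is followed directly by a model for score changes: "Changes in dependent outcome variables between baseline and follow-up at six months will be analysed by multiple linear regression models". Complications have no baseline value, so the section may have been written with effectiveness scores in mind, and a full analysis plan may hold a separate safety rule. This stands in part. It is a reason not to say that the authors chose intention to treat for harms. It is also why the lack of a binary or rate model is not raised here, since that is detail for a full plan. But the sentence as published covers all six-month data, and its conflict with the definition of conservative treatment lies within the article.

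**A reader might infer that the risk of surgery itself is understated.** The article does not support that. The rate within the surgical group stays at ps, unless crossovers carry a different risk. Only the contrast with conservative care shrinks.

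**A reader might also infer that never-operated patients dilute the surgical group,** and combine both crossover rates into 1 - 0.22 - 0.04 = 0.74. A patient planned for surgery who is never operated on has not begun the allocated treatment and, by the article's definition, is conservative. The exception largely removes such patients, so the 4% term drops out.

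**The initial-group comparison is legitimate.** It answers what follows from starting with one strategy or the other. Crossovers are a selected group, so a comparison by treatment received has its own bias. Both points stand and argue for showing the two analyses side by side. The type of complication is also recorded, so a surgical event in a crossover patient could be recognised, but the stated rule would still count it as conservative.

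**Conclusion.** The point holds in a limited form. Followed as written, the rule counts surgical complications after a late switch as conservative, against the article's own definition of that treatment. The excess complication risk of surgery over conservative care is then multiplied by 1 - c.

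The direction needs only that surgery carries more complications than conservative care. The size depends on c, which the article does not give for six months. The 22% is reported beside a two-year horizon and comes from another cohort. It may also include switches made before treatment began, which this article exempts. It is therefore an upper-end value, and a factor between 0.89 and 0.95 is more plausible than 0.78. The risk ratios of 4.2, 3.5 and 2.7 in place of 5 also rest on the assumed 15% and 3%, and on crossovers having the same surgical risk.

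This concerns a secondary outcome and leaves the ODI analysis untouched. It is a worthwhile, inexpensive correction.

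**What to change.** In Statistical Analysis, Outcomes:

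1. Keep intention to treat, with its present exception, for ODI and the other effectiveness outcomes.
2. State that complications are also reported by treatment actually received, with each event assigned to the treatment that preceded it, and that this is the primary presentation for attributing harm.
3. Show the initial-group comparison of complications beside it.
4. Reconcile this section with the definition of conservative treatment, so that it is clear where a patient operated on after starting conservative care belongs in each analysis.

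The cost is a few sentences, the dates of procedures and complications on the physician form if they are not already there, and one extra safety table. The groups in that table will differ from the effectiveness groups. Its comparison is open to selection, because patients who switch are not typical of those who started conservative care, and the report should say so.

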#### Costs

The most important cost predictors (including cost drivers) for total, direct, and indirect costs are identified by multivariate modelling approaches.

One multivariate modelling approach is to determine which individuals with CLBP are in the top, say, 15% of the total cost, and to contrast this group with the remaining individuals. The relevant cost predictors are identified by discriminant analysis, or any other suitable classification method such as logistic classification or classification trees.

Another approach is to model the costs by a multiple regression type model, where the costs are assumed to be log-Gaussian or gamma distributed. The uncertainty in the prediction of cost will be quantified by state-of-the-art methods [59,60].

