#### Inclusion and exclusion criteria

We defined broad inclusion criteria to ensure that the spectrum of patients represents the spectrum seen in routine settings: CLBP with a duration of the current episode of at least three months, no relevant improvement under prior conservative treatment for one year, patients about to undergo surgical or further conservative treatment, age 18–65 years at beginning of treatment, good understanding of German in the Swiss patient sample or English the New Zealand sample, and written consent (see table 1).

**Table 1 T1:** Inclusion and exclusion criteria

1. CLBP	7. specific CLBP
2. no relevant improvement under prior conservative treatment for one year	8. acute or subacute LBP
3. about to undergo surgical or further conservative treatment	9. comorbidity that determines overall well-being
4. age 18–65 years at the beginning of treatment	10. pregnancy
5. good understanding of German (CH) or English (NZ)	11. expected loss to follow-up
6. written consent	12. unwillingness to complete questionnaires

Exclusion criteria are specific CLBP (as infection, tumour, osteoporosis, ankylosing spondylitis, fracture, deformity, inflammatory process, and cauda equina syndrome), acute or subacute LBP (defined as LBP continuing for less than six respectively twelve weeks at beginning of treatment [1,4], comorbidity that determines overall well-being (e.g. painful/disabling arthritic hip joints), pregnancy, expected loss to follow-up (e.g. due to removal), and unwillingness to complete questionnaires (see table 1).

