#### Cost-utility

The socioeconomic objective of the study is to evaluate the cost-utility outcomes of surgical and conservative treatment of CLBP [8,9,27]. The costs considered include the direct health care expenditures borne by the health care system (insurance, public health care) and out-of-pocket expenditures by patients (medication, alternative medicine, personal prevention activities). The indirect social costs due to lost productivity because of absenteeism also will be accounted for [58]. Direct medical costs will collected from health insurance companies in CH, the NHS in NZ and the clinics in which the patients are selected. Indirect costs and out-of-pocket costs will be measured with a cost diary developed by the Zurich University of Applied Sciences in cooperation with the MEM Research Center. The cost diary will be kept by the patients on a weekly basis covering the total period of treatment with a maximum of six months. At beginning of treatment and end of follow-up period utility will be measured with an index based on EQol-5D and SF-36. Changes in the index will be translated into changes in QALYs.

The cost study of CLBP patients will concentrate on the segment of high-cost patients and address this question: Is this group homogeneous with respect to their socioeconomic status, care-seeking and back pain patterns? If the answer is no, are there subgroups whose cost may be reduced substantially by appropriate (nonmedical) support?

The cost-utility part of the study will be done in collaboration with the Zurich University of Applied Sciences, Institute of Health Economics.

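### The log-Gaussian or gamma assumption for costs does not fit indirect cost, which will be exactly zero for patients with no job or no absence; a model that keeps the zeros should be named

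*Protocol article*

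**What the plan says.** The Costs part of the Statistical Analysis section covers three outcomes: "The most important cost predictors (including cost drivers) for total, direct, and indirect costs are identified by multivariate modelling approaches". It offers two approaches. One classifies patients by "which individuals with CLBP are in the top, say, 15% of the total cost" and contrasts them with the rest. The other is a regression: "Another approach is to model the costs by a multiple regression type model", "where the costs are assumed to be log-Gaussian or gamma distributed". No separate provision is made for indirect costs.

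The Cost-utility section says what indirect cost is: "The indirect social costs due to lost productivity because of absenteeism also will be accounted for". The recording window is short: "The cost diary will be kept by the patients on a weekly basis covering the total period of treatment with a maximum of six months".

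On eligibility, the relevant criterion is "age 18–65 years at the beginning of treatment". None of the listed criteria requires a patient to be employed or off work. Work status and disability compensation status are recorded as baseline characteristics, so they are expected to vary.

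**The concern.** Read together, these sections give indirect cost a point mass at zero. A patient with no job has no absence to cost. A worker who loses no time within six months has none either. The two distributions named for the regression describe strictly positive amounts.

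This goes beyond a detail that a condensed article leaves out. The article states a distributional assumption that does not match its own definition of one of the three outcomes.

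What is at stake is the stated purpose of the regression, which is to find the predictors of cost. A treatment, co-intervention or compensation scheme can change indirect cost in two ways: by changing whether a patient loses any work time, and by changing how much is lost. A model confined to positive values sees only the second. Return-to-work programmes and duration of work absence, which the outcome analysis ranks among its highest priorities, could plausibly act through the first.

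**Working it through.** **Inputs from the document.** The outcomes, the distributions, the definition of indirect cost and the entry criteria are as set out above. The article gives no share of patients with zero indirect cost and no cost figures, so every zero share below is an assumption. The expected number analysed comes from the Feasibility section and reproduces: 2200 × 0.75 = 1650; 1650 × 0.60 = 990; 990 × 0.80 = 792.

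**Step 1: the two distributions at zero.** The log of zero is undefined, and the log-Gaussian log-density at zero is minus infinity. The gamma log-density at zero is plus infinity for shape below 1, finite only at shape 1, and minus infinity for shape above 1. Neither family gives zero any probability.

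**Step 2: patients concerned.** With zero share p0, the number with zero indirect cost is 792 × p0:

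| Assumed p0 | Zero cost | Left if zeros were dropped |
|---|---|---|
| 20% | 158 | 634 |
| 40% | 317 | 475 |
| 60% | 475 | 317 |

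**Step 3: mean indirect cost if zeros were dropped.** The true mean is (1 − p0) × the mean among positives, so the positives-only mean is too large by 1/(1 − p0):

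- p0 = 10%: 1/0.9 = 1.11
- p0 = 20%: 1/0.8 = 1.25
- p0 = 40%: 1/0.6 = 1.67
- p0 = 50%: 1/0.5 = 2.0
- p0 = 60%: 1/0.4 = 2.5

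**Step 4: predictor effects.** Take two equal groups with the same cost distribution among patients who have any cost. The true ratio of mean indirect cost is then (1 − p0 in group 2)/(1 − p0 in group 1). For zero shares of 50% and 30% this is 0.70/0.50 = 1.40. For 30% and 50% it is 0.50/0.70 = 0.71.

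This was simulated with 200 data sets of 792 patients per scenario. Positive costs were gamma with shape 1.5 and mean 8000 (both assumed). Average estimated ratios:

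| Zero share, group 1 v 2 | True ratio | Gamma, zeros dropped | Log-Gaussian, zeros dropped | Gamma log link, zeros kept | Two-part |
|---|---|---|---|---|---|
| 50% v 30% | 1.40 | 1.01 | 1.01 | 1.42 | 1.42 |
| 50% v 20% | 1.60 | 1.00 | 1.00 | 1.60 | 1.60 |
| 30% v 50% | 0.71 | 1.00 | 1.00 | 0.71 | 0.71 |

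With equal zero shares in both groups (20%, 40% or 60%) the true ratio is 1, and both models with zeros dropped gave 1.00 to 1.01. The bias in ratios therefore appears only when the predictor is related to the chance of a zero.

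The zeros-kept column is a gamma regression with log link fitted through its mean and variance equations. It accepts a zero outcome and recovers the true ratio.

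**The case against.** A reader might infer that patients with zero indirect cost will drop out and that the indirect-cost results are therefore biased. The article does not support that. It states no exclusion and no added constant, so the effect of dropping zeros is a consequence of one possible handling and not of a stated rule.

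A reader might also infer that neither named model can be fitted to these patients. That is true of the log-Gaussian model and of the full gamma likelihood, but not of every gamma fit. The quasi-likelihood version above keeps every patient and does as well as the two-part model on the ratio. A two-part model is thus one sound choice and not the only one.

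The bias is also conditional, as the equal-share scenarios show, and the overstated mean matters only if a positives-only mean is reported as the mean of all patients. The regression's stated purpose is to identify predictors. The article does not say that its fitted means feed the cost-utility comparison, so an effect on Hypothesis 3 cannot be asserted.

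Finally, the handling of zeros is often left to an analysis plan, and a plan that is not shown may already deal with it. These limits stand and narrow the point. They do not remove it: the article assigns a strictly positive distribution to an outcome that its own definition makes zero for some patients, and the log-Gaussian option cannot be applied to them without an unstated device.

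**Conclusion.** The point holds in a limited form. For indirect costs, in the regression that is one of the two cost approaches, the stated distributions do not accommodate exact zeros that the article's own definition and entry criteria lead one to expect.

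If zeros were dropped, the consequences could be large: a mean 1.25 times too high at 20% zeros and 2.0 times at 50%, and a true ratio of 1.4 reduced to about 1.0 when zero shares are 50% and 30%. These figures rest on assumed zero shares and, for the ratio, on equal cost among patients with any absence. Predictors unrelated to having any absence keep unbiased ratios.

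The top-15% classification uses total cost and is not affected, nor is the ODI primary endpoint. Direct and total costs should seldom be zero in treated patients. This is a secondary analysis that should be corrected, and it does not threaten the study's main conclusion.

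**What to change.** For indirect costs only, replace the log-Gaussian or gamma assumption with a model that keeps all patients. Either of these would do:

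- A two-part model: logistic regression for having any indirect cost and a gamma model with log link for the amount among those who have some, combined into a mean per patient that includes the zeros, with bootstrap intervals.
- A gamma log-link model fitted by quasi-likelihood to all patients, zeros retained, with robust standard errors.

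Name the choice before the cost data are seen. Keep the stated models for direct and total costs where all values are positive.

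The cost is a change of wording and slightly more modelling, with no new data. The two-part model gives two coefficients per predictor, which must be combined to express one effect on mean cost. The quasi-likelihood model avoids that, but does not separate the chance of any absence from its amount.
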